### Statistical Analysis

Quantitative data will be analyzed with descriptive statistics, paired *t* test, and chi-square tests using SPSS Statistics for Windows (Version 25; IBM Corp) [64]. Descriptive data will be presented as numbers and percentages. Paired *t* test will be used to assess the differences in the mean scores of each of the outcome scales for the baseline and the follow-up time points. In addition, the chi-square test will be used to compare the prevalence of burnout, likely GAD and likely MDD, from baseline to the follow-up time points.

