## Methods

### Study Design

This is a quantitative longitudinal study with data collected from subscribers of the Wellness4MDs program using a web-based survey at the onset of the program and at designated follow-up timepoints. The surveys will include questions related to sociodemographic characteristics, roles, years of training, specialty, work, and clinical information. The Wellness4MDs program will deliver daily supportive and informative SMS text messages with or without embedded web links for mental health support or literacy resources to subscriber cell phones for 6 months. Participation in the surveys would be voluntary, and nonparticipation in any of the surveys will not impact program participation or service delivery. The Wellness4MDs is a national collaborative project that will leverage stakeholder partnerships to disseminate the program to physicians, postgraduate trainees, and medical students. Potential collaborating organizations include the Royal College of Physicians and Surgeons of Canada, faculties of medicine across Canada, provincial medical associations, provincial health authorities, and provincial medical licensing colleges. Initially, promotional material will be provided and give an overview of the Wellness4MDs program and information about how physicians, postgraduate medical trainees, and medical students can subscribe and unsubscribe to the program. Collaborating organizations will be requested to share information about the Wellness4MDs program with physicians, postgraduate medical trainees, and medical students on their databases and social medical handles, including Facebook, LinkedIn, Instagram, and Twitter (rebranded as X). Thus, the Wellness4MDs recruitment plan will mirror the successful recruitment plan of similar programs in Alberta, including the Text4Hope program that was launched in response to COVID-19 in March 2020 [36,37,43] as a collaborative initiative between the University of Alberta, Alberta Health Services, and six health foundations. Text4Hope was the subject of a wide-exposure communications campaign (television, radio, internet, and print media), including the local provincial mental health foundation, Alberta Health Services, and a media release by the provincial chief medical officer [44].

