### Wellness4MDs Program

The Wellness4MDs program is modeled on the highly successful Text4Hope and Wellness4Teachers initiatives in Canada [35,47]. The program is powered by the ResilienceNHope software, a web-based application that delivers the suite of supportive SMS text and email messaging programs, including Text4Mood, Text4Hope, Wellness4Teachers, Text4PTSI, Text4Wellness, and MoreGoodDays [48]. Canadian physicians, postgraduate trainees, and medical students will be able to subscribe to the Wellness4MDs program by texting “WellMD” to a designated phone number. Individuals can unsubscribe to the program by simply texting “stop” to the program phone number. The Wellness4MDs program will deliver daily supportive and informative SMS text messages (some with embedded web links for mental health support or literacy resources) to subscriber cell phones for 6 months. The Wellness4MDs program SMS text messages are based on CBT principles and were developed by psychiatrists, mental health therapists, clinical psychologists, and users of mental health services. About a third of the SMS text messages will have embedded web links that include additional physician health and wellness resources from reputable sources.

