### Hypothesis

We hypothesize that the Wellness4MDs program will achieve (1) at least a 20% reduction in mean scores for burnout, anxiety, and depressive symptoms on validated scales and a 20% increase in self-reported well-being at 6 weeks, 3 months, and 6 months after receiving the service, and (2) at least 80% of subscribers will express satisfaction with the program and perceive the daily supportive SMS text messages as contributing to their overall mental well-being.

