### Data Collection and Outcome Measures

The project will run for 3 consecutive years. Quantitative data will be collected from subscribers of the Wellness4MDs program using a web-based survey at the onset of the program (baseline), 6 weeks, 3 months (midpoint), and 6 months (end of service) as illustrated in Table 2. The surveys will include demographic questions such as sex and gender, as well as information about their role (physicians, postgraduate trainees, or medical students), their years of training or practice, and their specialty of retaining or practice if they are residents or physicians, in addition to the clinical outcome measures.

Primary outcome measures include changes in the mean scores on the PHQ-9 [51], the GAD-7 [52], the Maslach Burnout Inventory (MBI) [53], and the World Health Organization-Five Well-Being Index (WHO-5) [54] for subscribers from baseline to 6 weeks, 3 months, and 6 months.

The PHQ-9 is a self-administered scale designed to measure likely depression. It is an effective tool for patients and a validated tool for screening of depressive symptoms among the general population [55]. Symptoms experienced by patients during the 2 weeks before answering questionnaires are considered. Scores range from never (0), several days (1), more than half of days (2), to 3 (nearly every day), with every item ranging from 0 to 27 [51,56]. The tool’s reliability and validity have shown good psychometric properties with accepted sensitivity using 10 or above as a cutoff score and high internal consistency (Cronbach α=0.79) [55,57].

The GAD-7 scale is a self-administered valid tool designed to measure likely anxiety [58,59]. The 7 self-reported items are used to assess the severity of generalized anxiety disorder (GAD) symptoms over the past 2 weeks. Ratings are based on a 4-point Likert scale: not at all sure (0), several days (1), over half the days (2), and nearly every day (3). The scores ranged from 0 to 21, with higher scores indicative of more severe symptoms. A sensitivity of 89% and a specificity of 82% for a cutoff score of 10 [59] are considered. The GAD-7 also showed good test-retest reliability (intraclass correlation 0.83), as well as excellent internal consistency (Cronbach α=0.92) [58,60].

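### Separate paired t tests on voluntary follow-up surveys analyse a different set of responders at each wave; a likelihood-based mixed model should be the main analysis, with its own missing-data assumption stated and tested

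*Protocol article*

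**What the plan says.** All references are to the protocol article.

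- **Statistical Analysis.** The sentence that lists the methods begins "Quantitative data will be analyzed with descriptive statistics, paired". Besides descriptive summaries, only a paired t test and a chi-square test are named. The former is the one that "will be used to assess the differences in the mean scores of each of the outcome scales", with each follow-up set against baseline. No repeated-measures method is named.
- **Data Collection and Outcome Measures.** The primary outcomes are changes in mean PHQ-9, GAD-7, MBI and WHO-5 "for subscribers from baseline to 6 weeks, 3 months, and 6 months".
- **Study Design.** "Participation in the surveys would be voluntary, and nonparticipation in any of the surveys will not impact program participation or service delivery".
- **Ethical Considerations.** Participants receive no compensation or incentive.
- **Sample Size Calculation.** 1053, from an effect size of 0.1, variance 1, two-sided alpha 0.05 and 90% power.
- **Hypothesis.** One claim covers all three follow-up times for the scales. A second is that "at least 80% of subscribers will express satisfaction with the program". Table 2 schedules the satisfaction survey at the three follow-ups only.
- **Limitations of the Study.** Selection into subscribing is discussed. Loss to the follow-up surveys is not.

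**The concern.** A paired t test takes two occasions, so three follow-up waves mean three tests per scale. Each is restricted to people with baseline and that wave. Two consequences follow.

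First, the three estimates belong to different sets of responders, although the hypothesis reads them as one course over time. The 6-month estimate also ignores what people missing at 6 months reported at 6 weeks and 3 months.

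Second, the paired change estimates the change for everyone enrolled only if response is unrelated to the scores. Suppose people who scored worse at the previous survey answer less often. Those who remain then have unusually low earlier scores and drift back towards the mean, which hides improvement. If people who scored better stop answering, the drift exaggerates improvement. The planned effect is only 0.1 SD, so a modest distortion matters.

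**Working it through.** **1. The plan's own figure.** For a paired comparison, n = ((z0.975 + z0.90)/0.1)² = ((1.960 + 1.282)/0.1)² = 1051. The noncentral t gives 1053 (power 0.9001), so the figure reproduces. It is a count of complete baseline/6-month pairs and needs the variance of the difference to be 1. With unit SD at each time that variance is 2(1 - ρ), so 2(1 - ρ) = 1 gives ρ = 0.5. This is the baseline to 6-month correlation consistent with the plan, if the SD is 1.

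**2. Assumptions, none from the article.** 1500 people at baseline. Wave-to-wave retention is 70%, 80% and 80%, so 0.70 × 0.80 × 0.80 = 44.8% answer at 6 months. Dropout log-odds change by 0.3 per SD of the last observed score. The true 6-month change is -0.10 SD. Three correlation patterns are compared:

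- AR(1) with 0.5 to 0.6: the baseline to 6-month correlation is 0.5³ = 0.125 to 0.6³ = 0.216, so the difference variance is 1.75 to 1.57.
- Constant 0.5, as in step 1.
- Constant 0.83, the GAD-7 test-retest value in Data Collection and Outcome Measures. As a short-term figure, it is an upper bound.

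**3. Dropout driven by the last observed score: estimated 6-month change (truth -0.10).**

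| Correlation | Paired, worse scorers leave | Paired, better scorers leave | Bias of paired test | Mixed model |
|---|---|---|---|---|
| AR(1) 0.5 to 0.6 | -0.02 to -0.03 | -0.17 to -0.18 | about 0.07 to 0.08 | about -0.10 |
| Constant 0.5 | -0.06 | -0.14 | about 0.04 | about -0.10 |
| Constant 0.83 | -0.085 | -0.115 | about 0.015 | about -0.10 |

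**4. Random dropout.** Both methods are unbiased. Under AR(1) the standard errors are 0.0514 (paired) and 0.0441 (model) at 0.5, so the model's variance is 1 - (0.0441/0.0514)² = 26% lower. At 0.6 they are 0.0489 and 0.0415, or 28% lower. With constant correlation the reduction is about 15 to 20% at 0.5 and 9 to 15% at 0.83. Overall it is roughly 10 to 30%.

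**5. Dropout driven by the current, unobserved score.** Same set-up, correlation 0.5 to 0.6, worse scorers leaving. The paired test gives about -0.13 to -0.14 and the model about -0.17 to -0.18. The bias is 0.03 to 0.04 for the paired test and 0.07 to 0.08 for the model.

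**6. Separate check with stronger dropout.** N = 1053, constant correlation 0.5, log-odds 0.7 per SD of the previous score, with about 71%, 52% and 39% responding. If worse scorers leave, the paired 6-month estimate is -0.014 and the model's -0.094. If better scorers leave, they are -0.186 and -0.099. In the first case the mean baseline score of those analysed moves from -0.18 SD (6 weeks) to -0.26 (3 months) and -0.33 (6 months), against 0 for all enrolled. That shows how the groups differ by wave. With no true change and worse scorers leaving, the paired test at 6 months rejects in 45% of runs.

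**The case against.** **The model can do worse.** Distress at the moment of the missed survey may be what keeps people from answering. Step 5 then applies, and the model's bias is about twice that of the paired test. The good results in step 3 are expected, because that dropout mechanism is the one the model assumes. This objection stands. It rules out presenting the model as a cure, and it is why a sensitivity analysis must go with it.

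**The size depends on the inputs.** Correlation, retention and dropout slope are all assumed. This also stands. A reader might infer that the bias is as large as the planned effect. The documents do not support that. In the main set-up the bias is 0.015 to 0.08 SD against 0.10, and about 0.09 with the stronger dropout in step 6. Passing 0.10 takes harsher assumptions still, for which the article gives no basis.

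**Other readings that go too far.** A reader might infer that anyone who skips a survey is lost altogether. Each test drops only those missing that wave, and 6-week and 3-month answers are used in their own tests. A reader might also count the text opt-out as survey dropout. However, "Individuals can unsubscribe to the program by simply texting" a stop word concerns the messages, and "nonparticipation in any of the surveys will not impact program participation or service delivery" shows that the article treats surveys and messages separately.

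**The details may be in an unseen analysis plan.** Missing-data handling may well be there, and its absence here is not the point. The choice of the paired t test for mean scores is written in the article. The abstract also mentions a cross-sectional controlled comparison, but that does not change how within-person change is to be analysed.

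**Satisfaction.** A mixed model for symptom scores does nothing for this hypothesis. A confidence-limit success rule, or counting all non-respondents as dissatisfied, would be a preference and not the correction of an error. Only the mismatch between subscribers and those who can be measured remains.

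**Conclusion.** The point holds in limited form. The article fixes a method that analyses a different responder group at each wave and is biased, in either direction, when response depends on earlier observed scores. Under the stated assumptions the bias is about 0.015 to 0.08 SD, and about 0.04 SD at the correlation that fits the planned 1053. A likelihood-based mixed model removes that bias and has roughly 10 to 30% lower variance under random dropout. Its advantage rests on dropout depending only on observed data. If dropout depends on the current score, it can be the more biased of the two. Baseline-only subscribers add little information on change, so the model does not restore lost power. Nor does it supply a control group. The change is worth making because it is cheap, but the true size of the problem cannot be known from the article.

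**What to change.** 1. For each scale, make a likelihood-based linear mixed model for repeated measures the main analysis: time as a factor, unstructured covariance, all subscribers with a baseline survey, and contrasts against baseline at 6 weeks, 3 months and 6 months. Do not use classical repeated-measures ANOVA, which deletes anyone missing any wave.
2. Keep the paired t tests as a sensitivity analysis.
3. State that the model assumes dropout depends on observed data only. Add a delta-type sensitivity analysis that shifts the unobserved scores over a stated range in both directions.
4. Reword the satisfaction hypothesis from subscribers to survey respondents, and report the response rate beside the result.

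Cost: analysis wording and a little more analysis work. No new data are needed, and the named software fits such models.

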**Methods:**

This longitudinal study represents a multistakeholder, mixed methods, multiyear implementation science project. Project evaluation will be conducted through a quantitative prospective longitudinal approach using a paired sample comparison, a naturalistic cross-sectional controlled design, and satisfaction surveys. Prevalence estimates for psychological problems would be based on baseline data from self-completed validated rating scales. Additional data will be collected at designated time points for paired comparison. Outcome measures will be assessed using standardized rating scales, including the Maslach Burnout Inventory for burnout symptoms, the 9-item Patient Health Questionnaire for depression symptoms, the 7-item Generalized Anxiety Disorder scale for anxiety symptoms, and the World Health Organization–Five Well-Being Index.

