### Sample Size Calculation

With a projection that the effect size for the reduction in mean 7-item Generalized Anxiety Disorder (GAD-7) scale and 9-item Patient Health Questionnaire (PHQ-9) scores at 6 months from baseline would be 0.1, a population variance of 1 for each scale mean score, a 2-sided significance level α=.05, and a power of 90% (β=.1), using a web-based script [51], we estimated that the sample size needed to assess the effects of the daily supportive SMS text messages on the outcome variables would be 1053.

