The WHO-5 is a self-reported measure of subjective well-being that is highly useful in clinical practice and in research studies to assess well-being over time or to compare well-being between groups [61]. The scale includes 5 positively worded items with a 6-point Likert scale used to assess participant’s feelings in the last 2 weeks, ranging from 0 (not present) to 5 (constantly present). The raw scores are transformed into a score from 0 (worst thinkable well-being) to 100 (best thinkable well-being) [62]. Having a score <50 indicates poor emotional well-being and requires further evaluation. The WHO-5 demonstrated satisfactory internal consistency reliability and concurrent validity with other scales [61,62].

**Table 2 table2:** Client-oriented outcome measures and feedbacks and experiences of clients and stakeholders.

Construct	Tool (scale)	T_0_^a^	T_1_ ^b^	T_2_ ^c^	T_3_ ^d^
Likely MDD^e^	PHQ-9^f^	✓	✓	✓	✓
Likely GAD^g^	GAD-7^h^	✓	✓	✓	✓
Burnout	Maslach Burnout Inventory	✓	✓	✓	✓
Mental well-being	WHO-5^i^	✓	✓	✓	✓
Satisfaction with the service	Standardized satisfaction survey		✓	✓	✓
Experience and feedback	Focus groups and key informant interviews				✓

^a^T_0_: baseline timepoint.

^b^T_1_: 6-week timepoint.

^c^T_2_: 3-month timepoint.

^d^T_3_: 6-month timepoint.

^e^MDD: major depressive disorder.

^f^PHQ-9: 9-item Patient Health Questionnaire.

^g^GAD: generalized anxiety disorder.

^h^GAD-7: 7-item Generalized Anxiety Disorder.

^i^WHO-5: World Health Organization-Five Well-Being Index.

The MBI, a short questionnaire-based tool, is designed to measure the symptoms and severity of burnout. In total, 3 main domains are examined, that are depersonalization, emotional exhaustion, and professional fulfillment index. The professional fulfillment index includes 2 domains, that are work exhaustion and interpersonal disengagement (Burnout scale) and the professional fulfillment scale. The reliability of MBI is supported by several studies, where Cronbach α ratings of 0.90 for emotional exhaustion, 0.76 for depersonalization, and 0.76 for personal accomplishment [63].

Secondary outcome measures include changes in prevalence in subscribers of burnout, likely GAD and likely major depressive disorder (MDD), from baseline to 6 weeks, 3 months, and 6 months measured using the GAD-7, the PHQ-9, and the MBI. Other secondary outcome measures include subscriber satisfaction.

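### Within-subscriber change in prevalence (a secondary outcome) is to be tested with an ordinary chi-square test, which ignores the pairing: p values come out too large and power is lost

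*Protocol article*

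**What the plan says.** The Data Collection and Outcome Measures section of the protocol article defines the endpoint within subscribers: "Secondary outcome measures include changes in prevalence in subscribers of burnout, likely GAD and likely major depressive disorder (MDD), from baseline to 6 weeks", and likewise to 3 and 6 months. Table 2 shows the PHQ-9, GAD-7 and Maslach Burnout Inventory administered at all four time points. The Methods paragraph of the abstract states the purpose of the follow-up surveys: "Additional data will be collected at designated time points for paired comparison".

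The Statistical Analysis section gives the complete list of methods: "Quantitative data will be analyzed with descriptive statistics, paired *t* test, and chi-square tests using SPSS Statistics for Windows". It then assigns them. For the scale scores, "Paired *t* test will be used to assess the differences in the mean scores of each of the outcome scales". For the yes/no outcomes, "the chi-square test will be used to compare the prevalence of burnout, likely GAD and likely MDD, from baseline to the follow-up time points". The word paired is attached to the t test only. McNemar's test, Cochran's Q, GEE and mixed models are not named anywhere in the article.

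**The concern.** The yes/no outcomes come from the same people as the mean scores, at the same times, yet only the mean scores get a method that uses the pairing. A Pearson chi-square test on a table of time by caseness counts one subscriber's two answers as if two unrelated people had given them. Its standard error leaves out the within-person covariance. When that covariance is positive, as is expected for symptom status over six months, the standard error is too large.

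What is at stake is the set of tests for change in prevalence: three conditions at three follow-up times. Reducing prevalence is half of the programme's stated objective (prevalence and severity). A modest real reduction could be reported as non-significant although the data collected were enough to show it.

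**Working it through.** **Inputs from the protocol article.** Two-sided α of 0.05, power 90%, effect size 0.1, variance 1 and N = 1053 (Sample Size Calculation). The article gives no assumption for prevalence, for change in prevalence or for within-person correlation.

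**Step 1: reproduce the plan's own figure.** For a paired (one-sample) mean, n = ((1.960 + 1.282) × 1 / 0.1)² = 1050.7, so 1051 by the normal approximation. The noncentral t calculation gives 1052.7, so 1053, which matches. Two independent groups would need 2102 per group. The sample size is therefore itself a paired calculation.

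**Step 2: assumptions.** 1053 complete pairs; baseline prevalence p0 = 40%; follow-up prevalence p1; phi between the two statuses 0.3 to 0.6. All of these except 1053 are illustrative.

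**Step 3: standard errors of d = p0 − p1.**
- P(case at both times): p11 = p0·p1 + phi·√[p0(1−p0)p1(1−p1)]
- Discordant proportion: D = p0 + p1 − 2·p11
- Used by the chi-square test: √[2·p̄(1−p̄)/N], with p̄ the mean of p0 and p1
- True: √[(D − d²)/N]
- Used by McNemar's test under the null: √[D/N]

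**Step 4: size when nothing changes.** With p0 = p1 the true standard error is √(1−phi) times the one the chi-square test uses, so true size = 2·[1 − Φ(1.96/√(1−phi))]. This does not depend on prevalence or on N.

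| phi | 1.96/√(1−phi) | True size at nominal 5% |
|---|---|---|
| 0 | 1.96 | 5.0% |
| 0.3 | 2.34 | 1.9% |
| 0.4 | 2.53 | 1.1% |
| 0.5 | 2.77 | 0.56% |
| 0.6 | 3.10 | 0.19% |

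Simulation (40,000 replicates) agrees, and McNemar's test stays at about 5% throughout.

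**Step 5: power with 1053 pairs.** Worked case, 40% to 36% at phi 0.5:
- p11 = 0.144 + 0.5 × √(0.24 × 0.2304) = 0.2616
- D = 0.76 − 0.5232 = 0.2368
- chi-square standard error √(2 × 0.38 × 0.62/1053) = 0.0212, so z = 0.04/0.0212 = 1.89, short of 1.96
- McNemar standard error √(0.2368/1053) = 0.0150, so z = 0.04/0.0150 = 2.67

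| Change | phi | Chi-square | McNemar |
|---|---|---|---|
| 40% to 36% | 0.3 | 46–47% | 61–62% |
| 40% to 36% | 0.5 | 46% | 76% |
| 40% to 36% | 0.6 | 46% | 85% |
| 40% to 35% | 0.3 to 0.6 | 69–74% | 81–96% |
| 40% to 32% | 0.3 to 0.6 | 99% or more | over 99% |

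As a second illustration, the Introduction quotes 53% with burnout symptoms in a national survey. For 53% to 48% at phi 0.5, power is 68% with chi-square and 90% with McNemar.

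**Step 6: incomplete follow-up.** Suppose all 1053 baseline responders are compared with m follow-up responders who are all among them. The true variance is then proportional to 1/1053 + 1/m − 2·phi/1053, while the chi-square test uses 1/1053 + 1/m. With m = 300 and phi 0.3, the ratio is 0.004283/0.003713 = 1.154. The effective critical value is 1.96 × √1.154 = 2.105, and true size is 3.5%. At phi 0.5 it is 2.6%. The distortion shrinks but remains.

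**The case against.** **It touches only secondary outcomes.** This stands. The primary outcomes are changes in mean scores, they get a paired t test, and the sample size rests on them. Baseline prevalence and its correlates, the first aim given in the Introduction, do not involve this test.

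**The error is in the safe direction.** This also stands. A reader might infer from an invalid test that false claims of benefit become more likely. With positive within-person correlation the opposite holds: the false-positive rate is below 5%. Only a negative correlation, implausible here, would reverse this.

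**Larger effects would still be found.** This stands in part. The article's only numerical target for symptoms is a 20% reduction, stated in the Hypothesis section for mean scores. If prevalence fell by the same relative amount, 40% to 32%, the chi-square test would have power of about 97% or more even at phi 0. The loss matters for modest changes with near-complete pairs.

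**The association reading.** A reader might fear a table of baseline status by follow-up status, where a significant association is mistaken for a change. The text does not support this: it speaks of comparing prevalence, which is a comparison of proportions.

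**Chi-square may loosely mean McNemar's, or may serve the other design component.** The abstract does list "a naturalistic cross-sectional controlled design, and satisfaction surveys", and an ordinary chi-square test would suit a comparison of new with existing subscribers. But the Statistical Analysis section ties the test to baseline against follow-up and attaches paired to the t test alone. If McNemar's test was intended, the same sentence needs correcting.

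**A condensed article leaves detail to a fuller plan.** This does not apply, because the test is named here rather than left open.

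**Conclusion.** The concern holds as a should-fix point on a secondary analysis. As written, the chi-square test does not match the paired data that the article describes. Its p values for change in prevalence will be too large whenever a subscriber's status is positively correlated over time. With 1053 complete pairs, 40% baseline prevalence and phi 0.3 to 0.6, true size is about 1.9% to 0.2% instead of 5%, and power for 40% to 36% is about 46% instead of 61% to 85%. The phi values, the prevalences and the completeness of the pairs are assumptions, since the article gives none of them. The penalty is slight for a change as large as 40% to 32%, and the distortion of size is smaller when few baseline responders return. Neither the primary mean-score results nor the baseline prevalence estimates are called into question.

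**What to change.** In the Statistical Analysis section, replace the chi-square test for baseline-to-follow-up change with McNemar's test on matched pairs. Report the paired risk difference with its 95% CI for each condition at 6 weeks, 3 months and 6 months. Alternatively, specify one logistic GEE or mixed model per condition with time as a factor, which uses all four waves and includes subscribers who miss some of them. Retain the chi-square test explicitly for comparisons between different people, such as roles or new against existing subscribers.

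The cost is one sentence. No new data are needed, and the paired t test already requires each subscriber's records to be linked. The change should be made before the prevalence comparisons are analysed.
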